# Improving Quality of ICD-10 (International Statistical Classification of Diseases, Tenth Revision) Coding Using AI: Protocol for a Crossover Randomized Controlled Trial

**DOI:** 10.2196/54593

**Published:** 2024-03-12

**Keywords:** International Classification of Diseases, Tenth Revision, ICD-10, International Classification of Diseases, Eleventh Revision, ICD-11, Easy-ICD, clinical coding, artificial intelligence, machine learning, deep learning

## Abstract

**Background:**

Computer-assisted clinical coding (CAC) tools are designed to help clinical coders assign standardized codes, such as the *ICD-10* (*International Statistical Classification of Diseases, Tenth Revision*), to clinical texts, such as discharge summaries. Maintaining the integrity of these standardized codes is important both for the functioning of health systems and for ensuring data used for secondary purposes are of high quality. Clinical coding is an error-prone cumbersome task, and the complexity of modern classification systems such as the *ICD-11* (*International Classification of Diseases, Eleventh Revision*) presents significant barriers to implementation. To date, there have only been a few user studies; therefore, our understanding is still limited regarding the role CAC systems can play in reducing the burden of coding and improving the overall quality of coding.

**Objective:**

The objective of the user study is to generate both qualitative and quantitative data for measuring the usefulness of a CAC system, Easy-ICD, that was developed for recommending *ICD-10* codes. Specifically, our goal is to assess whether our tool can reduce the burden on clinical coders and also improve coding quality.

**Methods:**

The user study is based on a crossover randomized controlled trial study design, where we measure the performance of clinical coders when they use our CAC tool versus when they do not. Performance is measured by the time it takes them to assign codes to both simple and complex clinical texts as well as the coding quality, that is, the accuracy of code assignment.

**Results:**

We expect the study to provide us with a measurement of the effectiveness of the CAC system compared to manual coding processes, both in terms of time use and coding quality. Positive outcomes from this study will imply that CAC tools hold the potential to reduce the burden on health care staff and will have major implications for the adoption of artificial intelligence–based CAC innovations to improve coding practice. Expected results to be published summer 2024.

**Conclusions:**

The planned user study promises a greater understanding of the impact CAC systems might have on clinical coding in real-life settings, especially with regard to coding time and quality. Further, the study may add new insights on how to meaningfully exploit current clinical text mining capabilities, with a view to reducing the burden on clinical coders, thus lowering the barriers and paving a more sustainable path to the adoption of modern coding systems, such as the new *ICD-11*.

**Trial Registration:**

clinicaltrials.gov NCT06286865; https://clinicaltrials.gov/study/NCT06286865

**International Registered Report Identifier (IRRID):**

DERR1-10.2196/54593

## Introduction

### Background

Artificial intelligence shows a lot of promise for many health care applications, but its implementation in clinical settings is still limited [1]. One promising implementation area is clinical coding, which involves clinical staff or trained personnel going through large amounts of clinical text, such as discharge summaries, and assigning clinical codes to the texts. Clinical staff can thus summarize the patient’s stay at the hospital using a system of codes such as the International Statistical Classification of Diseases and Related Health Problems (version 10; *ICD-10*[ *International Statistical Classification of Diseases, Tenth Revision*]) [2].

A systematic way of summarizing patient care at hospitals is important for multiple reasons. The primary use of such data is to judge both the quality and volume of care. The data also serve as a consideration point for resource allocation. In addition, good coding practice is important for improving the quality of data available for secondary purposes such as research and knowledge generation.

An analysis of the literature reveals at least 2 major uses for computer-assisted clinical coding (CAC) systems [3]. The first type of use is to assist clinical coders in their work in real time, while the other type of use is in auditing the quality of existing coding. Audits are a principal element of quality control, especially since there have been reports of significant coding errors in electronic health record (EHR) systems. For instance, in a Swedish study, Jacobsson and Serdén [4] reported that 20% of the main diagnosis codes were wrong. For this user study, we focus on the former type of use, that is, assisting clinical coders in real time.

### Available Knowledge

In terms of the informatics methods that CAC systems use, there is wide variation. Depending on specific use cases, rule-based methods have been successfully used to extract clinical concepts from texts [5-7] or to classify clinical texts into standard terminology such as Systematized Nomenclature of Medicine—Clinical Terms or International Classification of Diseases [8,9]. Rule-based methods appear to work well, but generally, texts have to be tokenized into short phrases or n-grams. Words within each sentence are usually treated independently of each other. Unless considered separately, clinical language peculiarities such as negation [10], uncertainty and speculations, and acronyms and abbreviations [11] can obscure the meaning of words in sentences.

With the advances in deep learning, in particular, transformer architectures, longer text sequences can be processed using contextual embeddings, where the representation of each word is based on its context. This contextual understanding of words makes deep learning an appropriate tool for CAC systems that process long and complex clinical texts. Santos et al’s [12] systematic review on the topic shows a clear timeline transition toward deep learning methods, and this finding is echoed in a recent review by Kaur et al [13]. However, occasioned by multiple limiting factors related to the nature of clinical coding, current state-of-the-art (SOTA) performance is still unsatisfactory and lags other application areas of deep learning.

One of the major limiting factors is that assigning clinical codes to large sequences of text is a hard problem, compounded by a very large number of codes that represent the label space (eg, more than 20,000 *ICD-10* codes for Norwegian). In addition to the large number of codes, the level of class imbalance is rather extreme in this use case. Another limiting factor is that many close codes have semantically similar descriptions. An example of 2 semantically similar codes is “Other diseases of tongue (K14.8)” and “Disease of tongue, unspecified (K14.9).” It is challenging for a model to discriminate the two, since they both appear to describe some unnamed condition of the tongue [14]. Combined with other limiting factors such as poor data quality and availability, these factors make the design of automatic *ICD-10* coding systems nearly unattainable, especially for minor languages such as Norwegian and Swedish.

To get around this automatic coding problem, 2 popular approaches have emerged. In the first approach, researchers experiment with just a small portion of the codes, for instance, top-10 [15] or top-50 codes [16]. In many instances, these few top-N codes represent the majority of the data, but such systems perform poorly on rare codes. In the second approach, rather than automatically assigning *ICD-10* codes, multiple possible codes are provided as suggestions, much like recommender systems, with top-N suggestions. It is conceivable that this second work-around approach is useful to clinical coders because it provides potentially meaningful cues and pointers to the correct codes. This is the approach taken by the current user study.

It is important to note that a number of inconsistent findings have emerged from the little that has been published. In a recent study, Chen et al [17] concluded that, while their system improved the accuracy of *ICD-10* assignment, the system did not reduce the time required to assign the codes. In complete contrast to these findings, an earlier study by Wang et al [18] found significant time efficiencies when the CAC system was used, as did Fung et al [19]. We hypothesize that text complexity partially explains the conflict. Since text complexity is a factor that has not been fully explored in existing studies, we base our analysis of accuracy and time on the complexity of the clinical text.

### Specific Aims

The aim of the project is to investigate artificial intelligence tools, natural language processing specifically, to improve the quality of *ICD-10* coding. The goal of the user study is to test whether our Easy-ICD system can reduce the burden of coding and also improve the quality of *ICD-10* coding. The main end points to measure are (1) the individual’s coding accuracy averaged across all instances and *F*_1_-score (harmonic mean of recall and precision, each of which is averaged over all instances), (2) time use for assigning codes, and (3) usability based on the system usability scale [20].

## Methods

### Study Population and Location

The user study will recruit clinical coders (physicians, health care staff, professional coders, etc) from Norway and Sweden on a rolling basis. Even though clinical notes are in Swedish, most of the target population understands both the Scandinavian languages.

### Inclusion and Exclusion Criteria

In terms of participants, the main inclusion criterion is that the participant has coded clinical texts before, preferably *ICD-10* coding. Participants could be clinicians, nurses, professional coders, or other health care staff who understand Swedish with any amount of coding experience. We shall exclude participants outside Sweden or Norway.

### Study Time Frame

Recruitment of participants commenced toward the end of 2023, and we will continue recruitment on a rolling basis until the target number of participants is reached.

### Ethical Considerations

The data curated for this study is available through Permission Dnr 2022-02386-02 from the Swedish Ethical Review Authority. This user study is part of the ClinCode Project approved by The Regional Committee for Medical and Health Research Ethics, Norway (260972). Participation is based on informed consent. A web page with information based on the template from the Norwegian Centre for Research Data is used to provide information about (1) purpose of the project; (2) institution responsible for the project; (3) why the user is being asked to participate; (4) what the user is expected to do as a participant; (5) participation as voluntary; (6) user personal privacy, when and what happens with their data; (7) information about user rights (under the General Data Protection Regulation); (8) who to contact for more information or concerns; and (9) the final section where the user clicks on “Consent” or “Decline.” If the user consents to participate, the consent is logged, and the user can proceed to the study. Thus, we have a written record of consent. If the user declines, they are redirected away from the study. It is important to note that no personal or identifying information is collected, and browser cookies are only used to track progress. Thus, all the data we store will be completely anonymous.

### Intervention

The CAC system, Easy-ICD, is based on deep learning transformer models, also called language models. The system uses a language model trained in 3 main cycles, based on a typical natural language processing pipeline involving unsupervised or semisupervised training (pretraining) and supervised training (fine-tuning). First, the base model, Kungliga Biblioteket—Bidirectional Encoder Representations From Transformers (KB-BERT), was obtained from the transformers library [21]. KB-BERT is a Swedish general language model that was pretrained by the National Library of Sweden [22] and is publicly available. This pretraining represents the first training cycle. In the second cycle, KB-BERT was further pretrained on 17.8 GB of pseudonymized Swedish clinical text from the Health Bank infrastructure at Stockholm University [11], resulting in the current clinical language model named SweDeClinBERT [23]. In the final training cycle, also called fine-tuning, the model was fine-tuned on a pseudonymized data set, the Stockholm EPR GastroICD-10 Pseudo Corpus II, encompassing 120,000 patients. Using pseudonymized data for training improves security by decreasing the likelihood of private information leakage.

This model achieves SOTA results on this clinical coding task, comparable to results reported for English health data sets like the Medical Information Mart for Intensive Care [24]. This clinical coding task is framed as a multilabel problem, where participants can select and assign more than one *ICD-10* code to the clinical text. Actual performance results of the model are reported in a paper under consideration, and these results will be released in the final reporting of the user study.

Considering the Easy-ICD user interface, instead of displaying only the top label or labels as predicted by the model, we display the top-N predictions, where N is between 5 and 10. Through experimentation, we determined that an ensemble output from the deep learning model and fuzzy logic had the best results. Fuzzy logic is based on word-level and sentence-level minimum edit distance, using Levenshtein distance [25], comparing between *ICD-10* descriptions and the clinical text.

Easy-ICD is implemented as a web application for this user study, but in the future, the functionality will be incorporated into an EHR system. We used the classical model-view-controller pattern involving the deep learning model module, HTML 5 web interface, and a Python back-end controller, respectively. The web interface has the following sections: (1) the clinical note, (2) color-coded visualization to explain the suggestions, (3) the top-N suggestions from where the participant selects relevant *ICD-10* codes to assign, (4) qualitative feedback with star-rating and text feedback, and (5) a lookup feature for *ICD-10* codes.

### Disease and Data

We use Swedish clinical notes in the gastrointestinal (gastro) domain in our study. The data used are from the gastrointestinal department of the Health Bank infrastructure at Stockholm University [11]. The data contain both in- and outpatient records of patients receiving treatment at the department, both surgery and other medical interventions. The data originate from a hospital, and no effort was made to include only similar cases; therefore, the cases vary.

The data are pseudonymized and have been curated by 2 professional clinical coders, so as to double-check the coding and create a gold standard. The 2 coders reviewed the data independently and reconciled their differences through discussion. This curation process also ensures that it will be possible to assign a code based on the clinical text alone, without the need for further information about the patient. This is important since the user study will not have access to further EHR data such as laboratory results or drug lists.

### Study Design

This study is designed as a 2×2 crossover study as illustrated in Figure 1. This design, AB|BA (2 different sequences and 2 periods), is chosen for its uniform and balanced properties, aiming to control the carryover effect between periods. The design is suitable not only for comparing treatments but also for assessing pre-post effect of an intervention [26]. In addition, the crossover design requires a comparatively smaller number of participants than what a randomized controlled trial would ordinarily require.

**Figure 1 figure1:**
[figure not shown]
Crossover randomized controlled trial where study participants are randomized into 2 groups. The first group first uses a control interface and then switches to our Easy-ICD tool, while the second group starts with our tool and switches to a control interface.

We will not incorporate a washout period partly because the learning element in the tasks measured is limited and partly because we do not want to risk losing participants in a long break between periods. The data sets in the 2 periods are different, and this limits any carryover effect in the sense that coders cannot memorize the text or the correct codes.

Once participants are recruited, they are randomly allocated to the 2 groups without allocation concealment. Allocation concealment will not be relevant for coders since it is known whether a participant is assisted or not, and we will not develop a placebo coding assistant. We will, however, conceal the allocation of subjects for the analyses.

In total, participants will code 20 clinical notes, where each note belongs to a single patient. The participants are asked to complete the experiment in 1 sitting without interruptions, and they cannot revisit or go back to previous notes. In the event that participants are interrupted, they are asked to exit the experiment, and any incomplete experiments are discarded as invalid.

In terms of the coding process, both the control and intervention user interfaces have a search utility for looking up *ICD-10* codes. Participants will be free to access any other additional search tools they wish to use without restriction. Since we measure time using a before and after design, the effect of additional tools is not expected to be a significant factor. The time is logged based on the browser button presses such as “Start,” “Next,” and “Complete.”

The user study process can be summarized in the following steps:

Study participants are randomly allocated to group 1 and group 2.To prepare participants for the experiment, a short video tutorial is played after the consent form is signed and right before the clinical coding task commences.In period 1 with 10 clinical notes, group 1 uses the control interface, while group 2 uses the intervention interface.Data are logged in the background using button presses—time, assigned codes, and comments.Then, there is an immediate crossover to period 2 for the last 10 clinical notes.Data continue to be logged in the background using button presses.At the end, participants in both groups will complete the system usability scale.

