### Measurements and Analyses

The focus of our measurements is on how clinical coders perform with and without our system:

Compared with the performance of the unaided user, statistical tests of significance are used to check whether there are significant differences in the quality of coding when Easy-ICD is used, as measured by accuracy and *F*_1_-score.Time spent is the time it takes for a clinical coder to assign a code.System usability survey will be given to all participants to measure usability of the web interfaces, both with and without our Easy-ICD system.

Main analyses are based on hypothesis testing using the paired *t* test and Wilcoxon test to compare the before and after means at a significance level of .05. Table 1 summarizes these hypotheses based on a test of equivalence.

**Table 1 table1:** Time use and coding quality hypotheses testing to compare the before and after means.

Time use		Coding quality (accuracy and *F*_1_-score)

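### The before-and-after argument does not neutralise unrestricted outside tools, and nothing keeps another automated coding assistant out of the control condition

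*Protocol article*

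**What the plan says.** All of this is in the protocol article.

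- **Access (Methods, Study Design).** "Participants will be free to access any other additional search tools they wish to use without restriction". The built-in lookup is common to both conditions: "both the control and intervention user interfaces have a search utility for looking up" codes.
- **Reason for not worrying (same paragraph).** "Since we measure time using a before and after design, the effect of additional tools is not expected to be a significant factor".
- **What is recorded (Study Design and its list of study steps).** "Data are logged in the background using button presses—time, assigned codes, and comments". Timing comes from the interface: "The time is logged based on the browser button presses such as" the start, next and completion buttons. Time spent in an outside tool is therefore inside the logged time and cannot be separated from it.
- **Comparator.** Measurements and Analyses sets Easy-ICD against "Compared with the performance of the unaided user". The Results part of the abstract promises "a measurement of the effectiveness of the CAC system compared to manual coding processes".
- **Design and analysis.** The design is an AB|BA crossover with 10 notes per period. The main comparison is a paired t test and Wilcoxon test at the .05 level, for time and for coding quality.

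**The concern.** Pairing removes what is constant within a coder, and balancing the two orders removes a common period effect. Neither removes something that moves with the interface. Outside-tool use may well do so, because one interface shows 5 to 10 suggested codes and the other shows none. Before-and-after is also a poor description of this design, since one of the two groups starts with Easy-ICD. The argument is made for time alone, although accuracy and F1-score are main end points too.

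The part that matters is narrow. The permission has no limit, so it does not rule out another automated coding or AI assistant. A coder who used one in the control period would no longer be coding manually. If such help worked, the difference between conditions would shrink for a reason unrelated to Easy-ICD. The article bases its conclusion on the significance of the time and quality tests, and the Discussion treats no improvement on either as a reason to rework the system.

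**Working it through.** **1. The plan's own figures.** The plan gives no figure for outside-tool use. Its only relevant number is the target of up to 30 participants. The effect sizes behind it are in Figure 2, which is not available here. With an assumed standardised paired effect of 0.8 and 80% power, a 2-tailed 5% paired t test needs 15, and doubling for two sequences (as the Sample Size Calculation says) gives 30. With 0.7 it needs 19, doubled to 38. So 30 fits one plausible set of inputs but cannot be confirmed. The point does not depend on it.

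**2. What the crossover cancels.** Let τ be the Easy-ICD effect, c the change in the outcome on a note where an outside tool is used, and pE and pC the shares of notes with such use under Easy-ICD and control. A coder's period mean is coder level + period effect + τ (if Easy-ICD) + c × p for that interface. In the within-coder difference the coder level drops out, and averaging the two sequences removes the period effect. What is left is

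expected difference = τ + c × (pE − pC).

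The second term is zero only if pE = pC or c = 0. The same holds for accuracy and F1-score, with c on that scale.

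**3. Illustration for time.** Assumed, not from the documents: τ = −20 s per note, and c = −30 s (the outside tool saves time) or +30 s (it costs time).

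| pC | pE | c = −30 s | c = +30 s |
|---|---|---|---|
| 0.5 | 0.5 | −20 + 0 = −20 | −20 + 0 = −20 |
| 0.6 | 0.2 | −20 + 12 = −8 | −20 − 12 = −32 |
| 0.8 | 0.1 | −20 + 21 = +1 | −20 − 21 = −41 |
| 0.2 | 0.6 | −20 − 12 = −32 | −20 + 12 = −8 |

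A simulated AB|BA trial (15 coders per sequence, 10 notes per period, 4,000 replicates) agreed with each of these values to within 0.2 s. Equal use cancels; unequal use does not, and the shift can go either way.

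**4. Which shifts are a problem.** If the outside tool is ordinary code search, a drop in its use under Easy-ICD is one way Easy-ICD works, and the whole expression is its total effect against coding with ordinary search. If the outside tool is another automated assistant used mainly in control, the extra term is contamination. When that assistant helps, the term works against τ, as in the second and third rows with c = −30 s.

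**5. What an opposing shift would do to power.** Assumed: 30 coders, paired t test, true standardised effect 0.7, shift expressed in SDs of the paired difference.

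| Opposing shift | Effect left | Power |
|---|---|---|
| 0 | 0.7 | 95.9% |
| 0.2 | 0.5 | 75.4% |
| 0.3 | 0.4 | 56.3% |
| 0.5 | 0.2 | 18.5% |

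These figures show sensitivity only. Nothing in the documents says that a shift of any given size will occur.

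**6. Could it be seen afterwards?** Time, assigned codes and comments are listed as logged. A coder might mention an outside tool in a comment, but nothing listed asks for it.

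**The case against.** The strongest reply is that the sentence states only an expectation about time, and that the sensible question is pragmatic: Easy-ICD against coding with whatever search coders like. On that view searching is a mediator, fewer searches are part of the benefit, and a null result means no detected gain over coding with freely chosen search tools. For ordinary searching this stands.

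Several stronger readings are tempting but not supported:

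- A reader might infer that any time saved through less outside searching is bias. It is not, for the reason just given.
- A reader might infer that the unaided user of Measurements and Analyses contradicts the open permission. In context the phrase can mean without Easy-ICD; even the control interface has a lookup.
- A reader might put a number on the dilution by supposing that some share of control notes is coded with an equally good assistant. The documents give no such share and no such benefit.
- A reader might infer that outside use is wholly invisible. Comments are logged, and a fuller protocol may record more.
- A reader might infer a privacy breach from notes being entered into other services. The article's remark on leakage concerns model training, and conditions of use on the information page are not shown.

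It is also fair that the permission speaks of search tools and does not name AI assistants. It does not exclude them either. That, and the faulty reason, remain.

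**Conclusion.** The point holds in a limited form. The stated reason is wrong as logic: the crossover cancels outside-tool use only when use is equal under both interfaces, and the reason does not reach accuracy or F1-score. The practical exposure is another automated coding assistant in the control period, which the wording leaves open and the listed log items would not capture systematically. This would weaken the comparison with manual coding that the abstract promises.

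The size and direction of any distortion are unknown, because no usage rates are given. The second and power illustrations rest on assumed effects and assumed usage. This does not show that the trial is biased or that a null result would be uninterpretable. It is a loose end that costs little to close.

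**What to change.** - Remove the before-and-after justification from Study Design.
- State that the comparator is coding without Easy-ICD, with ordinary code lookup and search allowed under both interfaces.
- Add one instruction line: participants should not use any other automated coding or AI assistant under either interface.
- After each 10-note period, outside the timed notes, ask one question on which outside tools were used, and report the answers by interface.
- Keep all coders in the main analysis. Any analysis that leaves out users of another assistant selects on behaviour after randomization, in a trial of at most 30, and should be labelled exploratory.
- Do not block copying from the note. That would hinder pasting terms into the lookup, probably more in control, and could itself inflate the apparent time saving.

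The cost is one instruction line and one untimed question per period, with no extra participants and no change to the timed tasks. The downside is slightly less freedom than in routine practice, and reliance on self-report.

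### The validity rule discards only incomplete sessions, so a coder who is interrupted but carries on to the end is kept, with the idle time counted as coding time

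*Protocol article*

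**What the plan says.** All the relevant rules are in the Methods section of the protocol article.

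- **One sitting.** Study Design: "The participants are asked to complete the experiment in 1 sitting without interruptions, and they cannot revisit or go back to previous notes".
- **Interruptions.** Study Design: "In the event that participants are interrupted, they are asked to exit the experiment, and any incomplete experiments are discarded as invalid".
- **Clock.** Study Design: "The time is logged based on the browser button presses such as “Start,” “Next,” and “Complete".
- **Log.** The numbered study steps: "Data are logged in the background using button presses—time, assigned codes, and comments".
- **Role of time.** Specific Aims lists time use as a main end point. The Results overview makes it one of the two tests on which the tool is judged. Principal Findings says that if accuracy does not improve, the time saving has to be significant.
- **Analysis.** Sample Size Calculation works with each coder's mean time per period, over about 10 notes. Measurements and Analyses names the paired t test and the Wilcoxon test at the .05 level.

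**The concern.** The authors plainly regard an interrupted session as unfit for the time end point, but the rule they wrote screens on something else. Leaving is a request to the coder. What triggers exclusion is incompleteness. A coder interrupted at note 15 can give up the whole session, or deal with the interruption and continue. The first choice is discarded and the second is kept. The rule therefore removes those who comply and retains those who do not.

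Time is taken from button presses, so an absence in the middle of a note lengthens that note's recorded time. The coder's summary is a mean over about 10 notes, so one long gap shifts the whole period mean. The crossover does not cancel this, because a gap falls in one period and hence under one interface. At stake are the precision of the time comparison and, if gaps are unevenly spread, its direction.

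**Working it through.** **Inputs from the protocol article.** 10 notes per period, up to 30 coders, 2-sided 5% level, paired t test and Wilcoxon test on coder means.

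**Inputs assumed, because the documents do not give them.** SD of paired differences 1 min/note; three of 30 coders (10%) with one unrecorded pause; pauses of 10, 20 or 30 minutes; standardized effects d of 0.5 and 0.7. The planned effect sizes are in Figure 2, which is not shown. The text places them from the upper part of medium to high, so d = 0.7 is nearer the planning range than d = 0.5.

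**The plan's own figure.** The target of 30 cannot be strictly reproduced without Figure 2. It is consistent with a paired t test at an assumed d = 0.8: n = 15 gives power 0.82, and doubling for two sequences gives 30. This point does not dispute that number.

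**Step 1: one pause.** Shift in a coder's period mean = pause / 10 notes. Pauses of 10, 20 and 30 minutes give 1, 2 and 3 min/note.

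**Step 2: noise.** Paired differences for 30 coders are drawn from N(d, 1). Three coders are shifted by plus or minus 1, 2 or 3, with the sign random because the period is random. 20,000 runs; the no-pause t-test values come from the noncentral t distribution.

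| Test | d | No pause | 10 min | 20 min | 30 min |
|---|---|---|---|---|---|
| Paired t | 0.5 | 0.75 | 0.71–0.72 | 0.61 | 0.48 |
| Paired t | 0.7 | 0.96 | 0.94 | 0.88 | 0.76 |
| Wilcoxon | 0.5 | 0.74–0.75 | 0.69 | 0.62–0.63 | 0.56 |
| Wilcoxon | 0.7 | 0.95 | 0.93 | 0.89 | 0.83–0.84 |

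Ranges are differences between runs. The Wilcoxon test loses less power when pauses are long, but it is not immune.

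**Step 3: bias if pauses follow time exposed.** Three 10-minute pauses shift the mean difference by at most 3 × 1 / 30 = 0.1 min/note. If each falls in control with probability c/(c + e), where c and e are the times per note with control and with the tool, the expected bias is 0.1 × (c − e)/(c + e). For an assumed saving of 0.5 min/note:

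- c = 5, e = 4.5: 0.1 × 0.5/9.5 = 0.005, or 1% of the saving
- c = 3, e = 2.5: 0.1 × 0.5/5.5 = 0.009, or 2%
- c = 2, e = 1.5: 0.1 × 0.5/3.5 = 0.014, or 3%

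**Step 4: bias if pauses cluster.** If all three 10-minute pauses fall in control, the estimated saving is 0.5 + 0.1 = 0.6 min/note. With no true effect and three 20-minute pauses all in one condition, the bias is 3 × 2 / 30 = 0.2 min/note, and type I error is about 0.11 for the t test and 0.09 for the Wilcoxon test.

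**The case against.** **Key links rest on silence.** A reader might infer that the software has no pause function and that the log could never reveal an absence. The article says neither. Its list of buttons is introduced as examples, and a fuller plan could contain a rule for idle or implausibly long note times. Note-level times are probably available, so a 30-minute gap on one note could be seen at analysis. This stands, and it limits the claim to what the written rule does. It does not remove the point: the article itself fixes a validity rule, and that rule does not catch interrupted sessions that are finished. Later cleaning can spot extreme values, but elapsed times alone cannot reliably separate an absence from a hard note.

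**The risk is addressed.** Coders are asked for one uninterrupted sitting and asked to leave if that fails. Nothing in the documents shows that many would ignore this. That is fair, and it is why the rate above is only an assumption.

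**The size depends on the reviewer's choices.** A reader might infer that the time saving would be overstated by 20%. That needs every pause to fall in control. Longer exposure under a slower interface gives only about 1–3%. Power also suffers much less at d = 0.7 than at d = 0.5, and the planned Wilcoxon test softens the effect of long pauses. All of this stands.

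**A tick-box is also self-report, by coders who know which interface they are using.** This stands too, and it is why an analysis keeping all times has to sit beside the one that drops flagged times. But ticking a box costs the coder nothing, whereas leaving costs the whole session.

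**Conclusion.** The point holds in limited form. By the stated rule, exclusion depends on incompleteness and interrupted coders are trusted to remove themselves. An interrupted coder who finishes is therefore kept, with the idle time inside an end point that helps decide the tool's value.

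The main consequence is noise, which makes a real time saving harder to detect. Under the assumptions above the loss runs from about 2 percentage points of t-test power (10-minute pauses, d = 0.7) to about 27 (30-minute pauses, d = 0.5). Material bias arises only if pauses cluster in one interface, and the documents give no reason to expect that beyond longer exposure. They do not support saying that the time comparison is invalid or that the tool's benefit will be inflated. This is a cheap improvement, not a flaw that undermines the trial.

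**What to change.** In both interfaces, put an untimed screen between notes. Next stops the clock and Start opens the following note, so a break between notes costs no recorded time. On that screen add a tick-box stating that the note just finished was interrupted.

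Keep the request for one sitting, but do not leave exit as the only response to an interruption. State in the plan that:

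- the codes of flagged notes are kept for accuracy and F1;
- time is analysed with flagged note times set to missing, alongside an analysis that keeps all times;
- the number of flagged notes is reported by interface.

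Recruitment is rolling and has begun, so apply the change to sessions from that date onward and identify the earlier sessions in a sensitivity analysis.

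The cost is one screen and one tick-box in the web application, and a few lines of analysis text. The downsides are one extra click per note, a slightly longer session, and continued reliance on self-report for pauses within a note.
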